### Randomization and Allocation Concealment and Blinding

Randomization will be achieved through a random sequence table generated by a computer (Excel software; Microsoft). The subject's randomization will be carried out by a researcher who will not enroll the participants, assign them to their groups, or perform outcome measurements. The researcher will conceal the distribution in an opaque envelope, which can only be opened after the subject has completed the baseline assessment. The subjects will be randomly assigned to three groups (allocation ratio 1:1:1). Only the researcher responsible for guiding the use of the app can know how the participants are allocated. The researcher responsible for the follow-up reviews will be blinded to the distribution at any time during the data collection period. Moreover, the group assignment will be blinded to the assessors and data analysts.

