### Inclusion Criteria

(1) Primary PD following the standard suggested by the Clinical Diagnostic Criteria for Parkinson's Disease in China (2016) (36);(2) Age of 50–70 years;(3) Meet the modified Hoehn–Yahr clinical grading criteria 1–2.5;(4) In stable condition with an essential dosage of madopar; and(5) Voluntary cooperation when training and signing the consent form.

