### Sample Size Calculation

Sample size calculations are based on the primary outcome measures of maximum excursion and directional control of limits of stability (LOS) measured using NeuroCom® Balance Master. Based on data provided by Li et al. (24), the primary outcome LOS was used to assess the maximum excursion and directional control in patients with PD (Cohen's *d* = 0.28, 15% improvement in maximum excursion, 12% improvement in directional control). For the current study, a similar effect size difference is anticipated between the balanced-enhanced experimental condition and the control condition. A smaller effect size difference is anticipated between the balanced-enhanced experimental condition and the basic experimental condition, hence the larger sample size. Based on sample size calculations (α = 0.05, β = 0.2), a total sample of 144 (assuming 15% attrition) will be sufficient to detect a small effect size (Cohen's *d* = 0.25) for between-group difference on the primary outcome if one exists.

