### Outcome Assessment

All participants' basic characteristics will be collected at baseline to describe the sample and study the characteristics related to the results. These baseline characteristics include age, gender, marital status, education, race/ethnicity, health status, medication use, resting blood pressure, weight (kg), and height (cm).

The experienced physical fitness assessors of the Shanghai University of Sport will assess all primary and secondary outcomes at baseline, 17 weeks (at the end of the intervention), and 33 weeks (follow-up 16 weeks later). The assessment process is shown in Table 1.

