### Statistical Analysis

Data will be analyzed in an open computing environment, R language, version 3.5.2. Differences between groups of baseline variables will be tested using the chi-square test (categorical variable) and one-way analysis of variance (continuous variable). Repeated measure ANOVA will be used to compare the changes from baseline to 16 weeks among the control group, basic experimental group, and balanced-enhanced experimental group. Pairwise comparisons between the balanced-enhanced experimental group and the two other groups will be conducted only if the omnibus F-test statistics indicated that the null hypothesis should be rejected. An independent sample *t*-test (95% confidence interval) will be used to compare group means. Paired *t*-tests will be used to examine changes within the groups from baseline to 16 and 32 weeks.

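### Disease stage is graded for everyone at screening but is used neither in the stated allocation nor in the between-arm comparison, an avoidable loss of precision and credibility though not a bias

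*Protocol article*

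**What the plan says.** All references are to the protocol article.

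- **Allocation** (Randomization and Allocation Concealment and Blinding): "Randomization will be achieved through a random sequence table generated by a computer (Excel software; Microsoft", and "The subjects will be randomly assigned to three groups (allocation ratio 1:1:1". Assignments sit in opaque envelopes opened after the baseline assessment. No stratum, block or minimisation factor is named.
- **Stage** (Inclusion Criteria): "Meet the modified Hoehn–Yahr clinical grading criteria 1–2.5". Every participant's stage is therefore known before allocation.
- **Baseline variables** (Outcome Assessment): "These baseline characteristics include age, gender, marital status, education, race/ethnicity, health status, medication use". The list continues with blood pressure, weight and height. Stage is not named.
- **Analysis** (Statistical Analysis): "Repeated measure ANOVA will be used to compare the changes from baseline to 16 weeks among the control group" and the two app groups. If the omnibus F-test rejects, the Tai Chi arm is compared with each of the other arms, and an independent-sample t-test is given for comparing means. No covariate is named. Baseline differences are tested, but nothing follows from the result.
- **Target** (Sample Size Calculation): the calculation takes α at 0.05 and power at 80%, allows 15% for dropout, and concludes that 144 patients in all "will be sufficient to detect a small effect size (Cohen's *d* = 0.25".
- **Prognosis** (Background): instability of balance is described as developing as the disease progresses.

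**The concern.** By the article's own account, stage bears on balance, and the primary outcome (limits of stability) measures balance. The trial holds the grade for everyone at no extra cost, yet the stated plan does not use it.

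With about 48 patients per arm, the mix of stages will differ somewhat between arms by chance. Three things are at stake:

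- The two Tai Chi contrasts carry noise that could be removed.
- If stage stays off the baseline table, a reader cannot see whether the arms were alike on it.
- If an imbalance does appear, any adjustment chosen after seeing it can be challenged as post hoc, because none was prespecified.

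**Working it through.** **1. The stated sample size.** This supplies the 0.25 used as a yardstick below. For two means, n per arm = 2(z₀.₉₇₅ + z₀.₈₀)²/d² = 2 × (1.960 + 0.842)²/0.25² ≈ 251.2, so 252. That is 756 in three arms. With 15% attrition, 252/0.85 gives 297 per arm, or 891. The stated 144 is not reproduced with d = 0.25. It is reproduced if 0.25 is read as Cohen's f for the between-group effect in a repeated-measures ANOVA (two measurements, correlation 0.5 assumed): 119 completers, so 40 per arm, 40/0.85 = 47.1, so 48 per arm and 144 in total. If only the Tai Chi arm differs, f = d√2/3, so f = 0.25 means d ≈ 0.53. This mismatch is a separate and larger issue. Here it matters only because the yardstick is uncertain.

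**2. Chance imbalance in stage.** From the documents: 144/3 = 48 per arm. Assumed: a share p = 0.5 of patients in the higher of two stage strata. The SD of the between-arm difference in that share is √(2p(1−p)/n) = √(2 × 0.25/48) = 0.102, so the 95% limit is 1.96 × 0.102 = 0.20, or 20 points.

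**3. Shift of a contrast.** Shift = imbalance × b, where b is the stage effect on the compared measure in SD units. The documents do not give b, so a range is shown.

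| b (assumed) | Typical shift (1 SD) | 95% limit | As % of 0.25 |
|---|---|---|---|
| 0.3 | 0.03 | 0.06 | 12 / 24 |
| 0.5 | 0.05 | 0.10 | 20 / 40 |
| 0.8 | 0.08 | 0.16 | 33 / 64 |

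With p = 0.3 and b = 0.5 the percentages are 19 / 37. With 41 completers per arm (144 × 0.85/3 = 40.8), p = 0.5 and b = 0.5, they are 22 / 43. Against d ≈ 0.53, the 0.10 SD limit is 0.10/0.53 ≈ 19%.

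**4. Which b applies.** Let stage shift limits of stability by b₀ at baseline and b₁₇ at week 17, and let Δ be the imbalance. A comparison of week-17 values shifts by Δ × b₁₇. A comparison of changes shifts by Δ × (b₁₇ − b₀), which is zero if the stage difference in level is stable. The ANOVA is stated on changes, so only a stage effect on change enters it. The text does not say whether the t-tests use changes or week-17 values. If week-17 values, the full b applies.

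**5. Bias or noise.** The full sampling error of a contrast at 48 per arm is √(2/48) = 0.204 SD, with a 95% limit of 0.40. The stage part is inside it: at b = 0.5 it is (0.051/0.204)² = 6.25% of the variance, which equals b²p(1−p). In 20,000 simulated trials, unadjusted type I error was 4.9% at b = 0.5 and 5.1% at b = 1.0, with a mean shift of about zero.

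**6. Gain from adjusting for stage.** At 41 per arm and b = 0.5, the SE falls from √(2/41) = 0.221 to 0.221 × √(1 − 0.0625) = 0.214, and power at d = 0.25 rises from 20.4% to 21.4%. At b = 0.8 (16% of variance) power is 23.4%. At b = 1.0 (25%) it is 25.7%.

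**7. Gain from the baseline value as a covariate.** With correlation ρ between baseline and follow-up, the variance factor is 1 − ρ² with the covariate and 2(1 − ρ) for change scores. At ρ = 0.5 that is 0.75 against 1.00, and at ρ = 0.8 it is 0.36 against 0.40 (ρ assumed).

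**The case against.** The best defence is that this is a condensed article. Strata, blocks and covariates may stand in a fuller protocol or analysis plan that is not shown. The baseline list is open-ended and includes health status. Severity is also restricted and measured: eligibility narrows stage to 1–2.5 and age to 50–70, and UPDRS-III and the Berg Balance Scale are taken at baseline. All of this is fair and limits the weight of the point. It does not remove it, because the article sets out the allocation method and the sequence of tests and gives stage no role in either.

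A reader might infer four stronger things that the documents do not support:

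- **That nothing in the analysis deals with stage.** The ANOVA compares changes from baseline, which cancels a stable difference in level.
- **That imbalance biases the result or swamps the effect.** It does not inflate type I error. The 40% figure is a tail case: an imbalance of 20 points or more arises in about 5% of allocations for a given contrast, and both the stage mix and the stage effect are assumed.
- **That the arms will miss 48.** Unrestricted allocation is not stated, and a shuffled list with 48 entries per arm fits the wording. Even under unrestricted allocation the mean variance cost is only about 1.5%.
- **That using Excel is a fault.** No defect in the sequence is shown.

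**Conclusion.** The point holds as a cheap improvement, not as an error that threatens validity. On the stated plan, a known prognostic grade plays no part in allocation, in the named baseline variables or in the between-arm comparison.

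With half the sample in the higher stratum and b = 0.5 SD, the shift of a contrast is typically about 0.05 SD and reaches about 0.10 SD at the 95% limit. Those figures apply in full only if the t-tests compare week-17 values. If they compare changes, b is the stage effect on change, which is probably smaller. The gain in power from adding stage is about 1 point at b = 0.5 and about 5 points at b = 1.0. The gain in credibility, from a visible baseline comparison and an adjustment fixed in advance, does not depend on these assumptions.

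**What to change.** 1. Add modified Hoehn–Yahr stage to the listed baseline characteristics.
2. Replace the unadjusted t-tests by a prespecified model for each primary measure (maximum excursion and directional control), with arm, the baseline value of that measure and stage stratum (1–1.5 versus 2–2.5). Take the pairwise Tai Chi contrasts and their 95% confidence intervals from that model. This also settles whether changes or week-17 values are compared.
3. If enrolment has not begun, stratify the sequence by the same two strata, using permuted blocks of randomly varied size and a separate envelope series for each stratum.

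Steps 1 and 2 use data already held and remain possible after enrolment starts, provided they are fixed before outcome data are examined by arm. Step 3 costs one extra envelope series and slight predictability at block ends, which varying the block size limits. No extra patients or visits are needed.

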### Intervention

The “Shoupa” app is an efficient medical and health service platform that can record patients' medications in real-time, aiming to manage PD better. The “Shoupa” app modules contain six sessions, prescription management, medication recording, effect recording, adverse report, patient's diary, and exploratory research. Persons with PD can easily submit their condition through the “Shoupa” app, and the professional triage consultant will arrange the most appropriate doctor to answer the question. In the “effect recording” section, patients can automatically generate historical reports based on the medication effect records and can conveniently customize historical reports through the date range. The “patient's diary” section provides a professional record template, and users can update their diary daily to control their physical state. The “medication recording” section provides users with convenient and intuitive medication reminders. Users can add medication records, set reminders based on prescriptions, and/or record each medication's effects. Besides, in the “exploratory research” part, the developer inserts oriented rehabilitation training videos (Tai Chi training) as needed to realize rehabilitation under the home condition. The “Shoupa” app software has been released as iPhone and Android apps.

During the recruitment process, all participants will see the registration screen of the application. However, after random assignment, participants will only be granted access to their assigned experimental group's features. To prevent interference between the control group, the basic experimental group, and the balanced-enhanced experimental group, participants will be instructed not to discuss their exercises during the experiment. A screenshot of the “Shoupa” app is shown in Figure 2.

**Figure 2 F2:**
[figure not shown]
“Shoupa” App intervention: **(A)** prescription management; **(B)** effect recording; **(C)** medication recording; **(D)** patient's diary; **(E)** exploratory research; **(F)** adverse report.

#### Control Group

Participants assigned to the control group will stay on the app's registration screen until the end of the 16-week study period. Therefore, they do not have the right to use any application functions that can help them improve their balance functions, so they will be encouraged to continue their daily activities.

#### Basic Experimental Group

Subjects who participate in the basic experimental group will get the self-monitoring function of using the app for daily medication management, but the “exploratory research” part of the function is prohibited. Members of the patient research team will organize persons with PD or their families to download the “Shoupa” app. Besides, the patients will perform a normal daily routine. For more information, the “Shoupa” app is presented in Supplementary File 1.

#### Balanced-Enhanced Experimental Group

Subjects participating in the balanced-enhanced experimental group are authorized to use the “exploratory research” function in addition to using the app for medication management. The “exploratory research” part is a set of simple Tai Chi training designed for persons with PD. The simple Tai Chi training is shown in Supplementary Figure 1. The training plan includes 60-min exercise classes, three times a week, for 16 weeks. Each session includes 40 min of the main training, 10 min of warm-up, and 10 min of finishing exercise. All exercises involve shifting the body's center of gravity (COG), as illustrated in Supplementary File 2. In addition to the therapist's guidance, each part of the app program contains a demo video and supporting subtitle text. The app program is connected to a website, and the clinician-side app can track the patient's training times through the website's background to monitor compliance with the plan. In other words, the “Shoupa” app records the training times the patient has watched the teaching course, but it is challenging to determine whether the patient is actually following the training. This requires the app to develop real-time video recording functions in future technological updates.

Every weekend during the intervention, the research team will arrange members to supervise and follow up on the participants to strengthen patients' compliance with home training. To confirm participant self-reported adherence to the study plan, patients' family members will be contacted through the phone to enquire weekly about patients' actual compliance. If participants experience dizziness, headache, or feel weak during the study, the intervention will be stopped immediately. After recovery, participants can therefore complete the interventions. If participants and their families need to consult any questions or have doubts during the study, they can always communicate with our team members. The research team will explain to the patients and their families in detail. Furthermore, the research team will count the participants who withdrew from the study and the reasons for the withdrawal.

### Outcome Assessment

All participants' basic characteristics will be collected at baseline to describe the sample and study the characteristics related to the results. These baseline characteristics include age, gender, marital status, education, race/ethnicity, health status, medication use, resting blood pressure, weight (kg), and height (cm).

The experienced physical fitness assessors of the Shanghai University of Sport will assess all primary and secondary outcomes at baseline, 17 weeks (at the end of the intervention), and 33 weeks (follow-up 16 weeks later). The assessment process is shown in Table 1.

#### Primary Outcomes

The LOS is used to assess postural stability in this study. The LOS test requires each participant to intentionally displace the COG to their stability limits without losing balance. Reduced LOS can affect people's ability to complete activities of daily life that involve turning, leaning, or bending over (37) and has been associated with an increased risk of falls in several groups of patients, including the elderly and patients with neurological diseases, such as PD (38, 39).

We will assign a professional technician to perform the Balance Master® balance training tester (NeuroCom) to assess the LOS (40). These two factors will be included: (1) maximum excursion and (2) directional control.

The maximum excursion is a measure of stability. When the person tilts the body to the theoretical limit (100%) in each of the eight target directions without falling, the limit of active movement is evaluated. The average of the eight target directions (expressed as a percentage of LOS) will indicate the persons' maximum excursion during the task, and the higher percentage indicates the maximum degree of the excursion.

Directional control measures the body movement accuracy by comparing the linear distance to the desired direction (toward the target) and the persons' movement's actual path. Measurement results are expressed as a percentage (%), where a higher value indicates higher accuracy toward the intended target.

#### Secondary Outcomes

The Unified Parkinson's Disease Rating Scale III (UPDRS-III) commonly used in clinical practice, including 14 items, will evaluate persons' exercise capacity with PD (41); the score ranges from 0 to 56, with higher values indicating more severe movement disorders. The Berg Balance Scale (BBS), which has 14 items, will assess balance ability; the score ranges from 0 to 56, with higher values indicating better balance ability (42, 43). The BBS is used in clinical practice and shows that it is reliable, valid, and sensitive. It is currently the most widely used clinical balance scale at home and abroad (44). Functional Reach Test (FRT) assesses the maximum distance that the participant stretches forward beyond the arm length, while the patient maintains a fixed standing position during the test (45); the average of the two trials will be used; a higher score indicates better balance ability (42). Timed Up & Go (TUG) assesses the time to rise from a chair, walk 10 feet, return, and sit down (46); the lower the score, the better the mobility. The 6-Minute Walk Test (6MWT) as the name depicts assesses the distance patients can withstand walking faster within 6 min. This test can comprehensively evaluate the exercise ability of patients with chronic diseases (47). The 39-item Parkinson's Disease Questionnaire (PDQ-39) evaluates the quality of life of persons with PD. The questionnaire consists of 39 questions (eight dimensions), which reflect the quality of life of persons with PD within the past 1 month, and higher scores indicate the worse quality of life (48).

### Adverse Events

All adverse events reported during the study will be recorded on the case report form (CRF). For this trial, adverse events will be defined as any unfavorable and unexpected signs, symptoms, or diseases related to the intervention, such as falls, fractures, dizziness, and hypertension. Researchers will ask participants about the adverse events they experienced before training begins and will record all the intervention's adverse events. Participants will be phoned and asked weekly about any experienced adverse events. Subjects will also be required to report any adverse events throughout the study protocol spontaneously. A serious adverse event (SAE) will be notified to the principal investigator within 24 h. The principal investigator is responsible for managing the safety report. Any adverse events related to the intervention will be reported to the ethical review committee of the Shanghai University of Sport. Although this committee is from the same institution as the authors, the ethics committee membership is independent of the investigators. None of the investigators are members of the ethics committee.

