### Participants and Recruitment

This study will recruit 144 eligible participants from the neurology clinic of Shanghai Tongji Hospital. Eligible persons with PD must meet the following inclusion criteria. The consort diagram of participant recruitment is shown in Table 1. We intend to distribute leaflets in the neurology clinic, and the neurologist will introduce and publicize the content of this study. Members of the research team will register participants interested in this training program and conduct corresponding screening evaluations. After the baseline assessment, eligible participants will be randomly assigned to one of three study groups.

**Table 1 T1:** Schedule for data collection, the process of the assessments per visits.

**Measures**	**Baseline (0 week)**	**Intervention period (1–16 weeks)**	**End of intervention (17 weeks)**	**Follow-up period (17–32 weeks)**	**Follow-up (33 weeks)**
Participants' characteristics	√				
Limits of stability (maximum excursion and directional control)	√		√		√
UPDRS-III	√		√		√
BBS	√		√		√
FRT	√		√		√
TUG	√		√		√
6MWT	√		√		√
PDQ-39	√		√		√
Adverse experiences^a^		√		√	
Combined medication^b^		√		√	

a *Adverse experiences: any adverse experiences at any visit during treatment sessions and 36 weeks will be monitored. The research team will review all trial protocols, monitor patient safety, and investigate any adverse events*.

b *Patients will be asked whether they have used other medications during the treatment. If they have used concomitant medications, then the type and dose of medication taken by them will also be recorded in detail*.

*UPDRS-III, Unified Parkinson's Disease Rating Scale III; BBS, Berg Balance Scale; FRT, Functional Reach Test; TUG, Timed Up & Go; 6MWT, 6-Minute Walk Test; PDQ-39, 39-item Parkinson's Disease Questionnaire*.

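### The adverse event definition requires unexpectedness and relatedness, conflicts with wider wording elsewhere, and if applied literally makes falls and injuries non-comparable between arms

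*Protocol article*

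**What the plan says.** The Adverse Events section opens with the recording rule: "All adverse events reported during the study will be recorded on the case report form (CRF"). The next sentence fixes the term: "adverse events will be defined as any unfavorable and unexpected signs, symptoms, or diseases related to the intervention", with the examples "such as falls, fractures, dizziness, and hypertension". It then states how events are found and kept:

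- "Researchers will ask participants about the adverse events they experienced before training begins", and they "will record all the intervention's adverse events".
- "Participants will be phoned and asked weekly about any experienced adverse events". Participants must also report events spontaneously.
- "Any adverse events related to the intervention will be reported to the ethical review committee".

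Footnote a of Table 1 (Participants and Recruitment) is wider: "any adverse experiences at any visit during treatment sessions and 36 weeks will be monitored". It mentions neither cause nor expectedness. The last scheduled assessment in that table is at week 33.

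On exposure, the Control Group section gives that arm no working app function. The Basic Experimental Group section gives medication self-monitoring without the Tai Chi module. The Balanced-Enhanced Experimental Group section adds three 60-minute Tai Chi sessions a week for 16 weeks, and names dizziness, headache and weakness as symptoms that may arise during the study.

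**The concern.** A definition decides what enters the safety data. Here an event must be unfavourable, unexpected and related to the intervention before it is an adverse event at all. Relatedness is normally a judgement made about an event already recorded. Used as an entry condition, it works differently in each arm, because the arms differ in whether there is any training to which an event could be related.

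Falls matter particularly. The Background links poor balance in Parkinson's disease to falls and fractures, the Primary Outcomes section cites fall risk as a reason for measuring limits of stability, and the Discussion credits Tai Chi with reducing falls. Yet no primary or secondary outcome counts falls. The adverse event record is the only place where the article says that they are captured. If that record is filtered by cause, it cannot show whether home Tai Chi raises or lowers falls relative to no training.

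**Working it through.** The article gives no event rate and no safety calculation, so there is no stated figure to reproduce. The check is textual, followed by an illustration.

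**Step 1. Apply the definition to each arm.**

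| Arm | Exposure | Ordinary fall at home | Foreseeable symptom such as dizziness |
|---|---|---|---|
| Control | No app function | Not related, so not an adverse event | Not related, so not an adverse event |
| Basic | Medication self-monitoring | Hardly related; only an app-related event could qualify | As for a fall |
| Tai Chi | Self-monitoring plus training | Qualifies if judged related and unexpected | Can be argued to be expected, yet dizziness is a listed example |

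**Step 2. Compare the definition with the other passages.**

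- If every adverse event is related by definition, the qualifier in "Any adverse events related to the intervention will be reported to the ethical review committee" is redundant. The sentence makes sense only if unrelated events can also be adverse events.
- Footnote a contains no filter on cause or expectedness.
- The weekly call is not limited by arm, but it asks about adverse events, which is the defined term.
- The recording rule "will record all the intervention's adverse events" points back to the narrow reading.
- The monitoring period in footnote a runs 36 − 33 = 3 weeks past the last visit.

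The article therefore supports both a narrow and a wide reading.

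**Step 3. Illustrate the literal reading.** Inputs: 144 participants (Sample Size Calculation) allocated 1:1:1 (Randomization), so 144/3 = 48 per arm, ignoring attrition. Assumptions not in the article: the true fall risk *p* is the same in every arm, between 10% and 40%. The expected number of fallers per arm is 48 × *p*. The p-values are two-sided Fisher exact tests of Tai Chi against control on rounded counts.

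| Assumed *p* | True fallers per arm | Control, literal rule | Tai Chi, literal rule | If all Tai Chi falls count |
|---|---|---|---|---|
| 10% | 4.8, about 5 | 0 | 0 to 5 | 5 v 0, p = 0.056 |
| 20% | 9.6, about 10 | 0 | 0 to 10 | 10 v 0, p = 0.001 |
| 30% | 14.4, about 14 | 0 | 0 to 14 | 14 v 0, p < 0.001 |
| 40% | 19.2, about 19 | 0 | 0 to 19 | 19 v 0, p < 0.001 |

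If half of the Tai Chi falls count, the result is 5 v 0 (p = 0.056) at 20% and 7 v 0 (p = 0.012) at 30%. The same true risk can appear as harm or as no events. Counting all events regardless of cause gives equal expected numbers in the arms, which is the truth assumed here. The basic arm is left out of the table because an app-related event could in principle qualify there.

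**The case against.** The strongest reply is that the article does not settle on the narrow reading. The weekly calls cover participants without regard to arm, footnote a is unrestricted, and the ethics-committee sentence seems to foresee unrelated events. A reader might infer from the definition that control-arm events cannot be counted at all. That goes too far: the documents are inconsistent, and staff following the footnote would count them. This part of the reply stands.

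The second reply is that falls and dizziness are named as examples, which is good evidence of what the authors meant to include, and that no passage classes any event as expected. The mention of dizziness, headache and weakness in the Tai Chi section is a management instruction, not a list of expected events. This weakens the argument that such events would be dropped, but does not remove it. The examples illustrate a definition that still requires unexpectedness and relatedness.

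Two further inferences are tempting and unsupported. One is that unblinded staff decide relatedness before an event is recorded. No passage says who judges it or when, and the blinding section keeps the follow-up researcher blind. The other is that the training is unsupervised. The Tai Chi section describes therapist guidance, weekend supervision and follow-up by the team, and weekly calls to family members.

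It is also true that the article states no safety hypothesis and that detailed harms reporting may sit in a fuller document. The point does not depend on that detail. It concerns a rule that the article states and then contradicts.

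**Conclusion.** The point holds as a conflict in the stated rules with a real consequence for safety data. The definition makes unexpectedness and relatedness conditions of being an adverse event, other passages assume a wider concept, and nothing says which governs. On the literal reading, ordinary falls and injuries in the control and basic arms would not qualify, and the between-arm comparison could not be interpreted. The illustrated gap is 0 in control against 0 to between 5 and 19 in Tai Chi when the true numbers are equal. That size rests on the assumed risks of 10% to 40%, on 48 per arm, and on literal application.

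A reader might infer that correcting the definition would let the trial rule out harm. It would not. At the assumed 20% risk, the 95% half-width for a risk difference is 1.96 × √(2 × 0.2 × 0.8 / 48) ≈ 0.16, or about 16 percentage points. The correction removes a source of bias but does not make the trial large enough to exclude harm. The primary efficacy analysis is unaffected. The change should be made, but the trial does not stand or fall by it.

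**What to change.** In the Adverse Events section, define an adverse event as any untoward medical occurrence after randomisation, in all three arms, regardless of cause or expectedness. Then:

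- ask the same scripted question of every participant at the weekly calls already planned;
- record relatedness and expectedness as separate fields on the case report form, completed after the event is captured;
- report events, including falls, by arm;
- keep the ethics-committee rule for related events, which then has a clear meaning as a subset;
- bring footnote a of Table 1 into line with the new definition, and reconcile its 36-week period with the week-33 last visit. The article does not show which figure is intended.

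The cost is an edit to the protocol and the case report form and slightly more events to record. It needs no new visits or calls.
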